### Statistical Methodology

#### Sample Size Calculation

The G*Power 3.1 (Heinrich-Heine-Universität Düsseldorf) program was used to determine the sample size. The calculation was based on the HADS total score, which is defined as the primary outcome of the study, assuming a repeated-measures design with 3 groups (home-based, face-to-face, and control) and 3 assessment time points (baseline, postintervention, and 4-week follow-up). Considering an α level of .05 and power of .80, an effect size of *f* of 0.25 (moderate) was assumed for the group × time interaction, with an assumed correlation among repeated measures of 0.50 and a nonsphericity correction (ε) of 1.0. Under these assumptions, a sample of at least 42 participants, randomized into the 3 groups, is required. This sample size was calculated to detect differences between groups and was not designed to formally demonstrate equivalence between the interventions. Anticipating a dropout rate of approximately 30% (18/60), a total of 60 participants will be recruited to ensure the necessary final sample size of 42 participants.

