#### Statistical Analysis

The analysis will be conducted using the ITT principle, including all randomized participants. Per-protocol sensitivity analyses will also be performed. For continuous variables, a linear mixed model will be used, with fixed effects for group (face-to-face, home-based, and control), time (baseline, postintervention, and follow-up), and group × time interactions. Participants will be modeled as a random effect. Baseline values will be included as part of the repeated-measures structure rather than as covariates, allowing the estimation of within- and between-group changes over time. Age and sex will be considered as covariates in adjusted models if baseline imbalances or clinically relevant associations with the outcomes are identified. The home-based vs face-to-face comparison will be interpreted based on effect estimates and confidence intervals and will not be treated as a formal equivalence analysis. This model, which treats repeated within-participant measures as a random effect, will be used. An appropriate covariance structure for the repeated measures will be selected based on model fit criteria. This method allows for the management of missing data under the assumption that they are missing at random. In cases of systematic losses, multiple imputations may be used as a complementary analysis.

For categorical or dichotomous variables, the chi-square or Fisher exact tests will be applied, where appropriate. For all hypothesis tests, the α level for statistical significance will be set at *P*<.0, corresponding to a 95% confidence level. To assess the magnitude of significant differences between the preintervention and postintervention moments and between groups, the Hedge *g* (x ®1–x ®2⁄ SD grouped) will be calculated. The effect size magnitudes will be interpreted as follows: <0.2, no effect; 0.2 to 0.4, small; 0.5 to 0.7, moderate; and ≥0.8, large [58]. Secondary outcomes will be analyzed using the same modeling strategy; however, these analyses will be considered exploratory, and no formal adjustment for multiple comparisons is planned. The data will be analyzed using IBM SPSS software, version 20.0, licensed to UDESC, and Microsoft Office Excel for Windows.

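### The fallback for systematic loss to follow-up is optional multiple imputation with no stated departure from missing at random, so it does not test the assumption it is set against

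*Protocol article*

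**What the plan says.** The primary outcome is HADS total, measured at baseline, after the programme and at the 4-week follow-up. Under Statistical Analysis, the protocol article specifies a linear mixed model with group, time and their interaction, on all randomised participants. Of missing outcomes it says: "This method allows for the management of missing data under the assumption that they are missing at random". The next sentence is the whole of the fallback: "In cases of systematic losses, multiple imputations may be used as a complementary analysis".

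Under Sample Size Calculation the planned loss is large: "Anticipating a dropout rate of approximately 30% (18/60), a total of 60 participants will be recruited".

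The other sensitivity analyses are a per-protocol analysis that drops major protocol deviators (Intervention Program, Statistical Analysis) and an exploration by adherence (end of Secondary Outcome Measures). Neither makes any assumption about the HADS scores of people who stop attending.

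**The concern.** The two sentences stand as a contrast: one tool for data missing at random, another for systematic loss. Read that way, the second tool should relax or at least vary the assumption of the first. As written it does not. Multiple imputation is a way of computing; what it assumes depends on the imputation model. No shift, reference-based rule or pattern-mixture model is stated, and no variable is named beyond those already in the mixed model. An analyst following the text would most naturally repeat the primary assumption.

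At stake is how the result is read. Unblinded participants report their own anxiety and depression, and up to 3 in 10 may be missing. If those lost from an active arm fare worse than their observed data predict, the mixed model overstates benefit, and a matching imputation result could be taken as support. The imputation is also optional, with no definition of when loss counts as systematic.

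**Working it through.** **The plan's own figure.** Required sample 42, planned loss 30% (Sample Size Calculation): 42 / (1 - 0.30) = 60, and 60 - 42 = 18 = 30% of 60. The 60 reproduces. The 42 is taken as given, because its derivation does not affect this point.

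**Does imputation from the same variables change the estimate?** This was checked by large-sample simulation with 300,000 per arm, in SD units. The assumptions, none of which comes from the documents except the 30% and the 0.5 correlation, were:

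- true active-versus-control effect 0.50 SD;
- baseline-to-post correlation 0.5;
- 30% loss in each arm;
- loss random in control, and in the active arm dependent on the unseen post score with log-odds of 0.5, 1.0 or 1.5 per SD.

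| Log-odds per SD | Mixed-model estimate | Imputation, same variables | Imputation plus auxiliary (correlation 0.5 with outcome) |
|---|---|---|---|
| 0.5 | 0.61 | 0.61 | 0.57 |
| 1.0 | 0.70 | 0.70 | 0.64 |
| 1.5 | 0.76 | 0.76 | 0.69 |

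The first two estimates agree and carry the same bias of 0.11 to 0.26 SD. An auxiliary variable removes only part of it.

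**When loss depends on a recorded auxiliary instead.** At the same three log-odds the mixed model gives 0.57, 0.63 and 0.66. Imputation using that auxiliary gives 0.50 each time, which is the true value. So imputation can help, but only if the right variables are in it.

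**Size of bias in general.** Let p be the share missing in an arm and delta the amount by which its dropouts do worse than missing at random predicts. Then

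bias in the contrast = p(active) x delta(active) - p(control) x delta(control).

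With p = 0.30 and delta(control) = 0:

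- delta 0.25 SD: 0.30 x 0.25 = 0.075, about 0.08 SD
- delta 0.5 SD: 0.30 x 0.5 = 0.15 SD
- delta 1.0 SD: 0.30 x 1.0 = 0.30 SD

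With equal p and equal delta in both arms the terms cancel. A separate simulation with equal outcome-dependent loss in both arms confirmed this: the true difference was 3.5 points, and both the mixed model and imputation gave 3.5.

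**What a delta-adjusted analysis shows.** In the middle scenario (mixed model 0.70, truth 0.50), adding 0.25, 0.5, 0.75 or 1.0 SD to imputed active-arm scores gives 0.62, 0.55, 0.47 and 0.40. The analysis does not reveal which delta is true. It shows how far the conclusion depends on missing at random, and the stated fallback does not.

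**The case against.** The best counter-argument is that the text leaves the imputation model open. Multiple imputation can be done under a not-at-random model, and the remedy proposed here is itself multiple imputation. A condensed article may leave such detail to an analysis plan. This stands against calling the planned imputation wrong in itself. It does not remove the mismatch in what is stated: a tool is offered for systematic loss with nothing that distinguishes its assumption from the primary model's.

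A reader might infer several stronger things that the documents do not support.

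- *That imputation could not correct the bias at all.* This fails if loss is explained by recorded variables outside the model. The trial collects session adherence, video-viewing analytics and weekly control-group contacts, some available even when a visit is missed.
- *That different dropout between arms is enough to cause bias.* It is not. Group is in the model, and so are HADS scores already observed. Only dependence on unseen scores that differs between arms biases the contrast, and the documents give no evidence of it.
- *That the effect would be overstated 1.43-fold (1/0.7), with 1.125 SD really 0.79 SD.* The 1.125 SD follows from f = 0.25 only if both active arms improve equally, control stays flat and the effect is kept at follow-up (f = 2d/9, so d = 0.25 x 9/2 = 1.125). The factor also needs every active-arm dropout to end at control level with no post-baseline data. Someone lost only at the 4-week visit still contributes a post-intervention score.
- *That the optional trigger opens the main result to choice after seeing the data.* The imputation is a complement and cannot replace the mixed model. The statistician is blinded until the primary analyses are complete.

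Scale also matters. With 14 completers per arm and correlation 0.5, the standard error of a pairwise difference in change is sqrt(2 x 1/14) = 0.38 SD, so a bias of 0.08 to 0.15 SD is under half a standard error. A bias of 0.30 SD is not negligible beside it.

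**Conclusion.** The concern holds in a limited form. As written, the fallback states no departure from missing at random and names no auxiliary variables, and neither the per-protocol nor the adherence analysis fills the gap. Agreement between the mixed model and imputation from the same variables would not show robustness to loss that depends on unseen HADS scores.

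Whether there will be bias is unknown. If 30% are lost in each arm and only active-arm dropouts deviate, it is about 0.08 to 0.30 SD for delta of 0.25 to 1.0 SD; it is near zero if the dependence is the same in both arms. The documents give no HADS standard deviation and no expected dropout by arm, so these sizes are scenarios, not forecasts. The primary model is not at fault. The change is worth making because planned loss is high and the remedy is cheap.

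**What to change.** Replace the sentence on systematic loss with a prespecified sensitivity analysis of HADS total that is run whatever the pattern of loss:

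1. Multiple imputation with named auxiliary variables recorded in the trial but not in the mixed model, such as session adherence.
2. Delta-adjusted imputation of missing post-baseline scores, with shifts set by arm (for example 0 to 1 SD towards worse scores), and/or control-based imputation in the active arms.
3. A report of the delta at which the active-versus-control conclusion changes, beside the number missing per arm and visit.

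The 0 to 1 SD range is a suggestion; the trial team can justify another, provided it is fixed before outcome data are seen. No extra participants or visits are needed. The cost is a little more analysis, one more table and possibly a less favourable statement about robustness.

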**Figure 3. F3:**
[figure not shown]
Schematic drawing of the in-person and home-based prehabilitation program protocol.

The primary outcome will be the total score of the Hospital Anxiety and Depression Scale (HADS). The HADS was developed in England [43] and was validated for Brazilian Portuguese by Botega et al [44]; the instrument showed internal consistency (Cronbach α) of 0.68 for anxiety and 0.77 for depression in its validation study. The instrument is a scale completed through an interview, preferably answered by the patient, and contains 14 questions, of which 7 assess anxiety (HADS-A) and 7 assess depressive symptoms (HADS-D). The scale emphasizes the psychological signs or consequences of anxiety and depression, excluding clinical symptoms such as dizziness and headache. The questions alternate, with half of them written in a positive tone and the other half in a negative tone. Each question is assigned a score from 0 to 3, with 3 indicating a state associated with more depressive symptoms or anxiety. Analyses of the HADS-A and HADS-D subscales will be conducted as secondary exploratory outcomes. In this study, HADS scores ≥8 will be used as a cutoff for each domain, as this is the score that indicates the presence of depressive and anxious symptoms and possible cases of depression and anxiety.

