## Discussion

This protocol for a randomized controlled trial (RCT) aims to evaluate the impact of face-to-face and home-based rehabilitation models, compared with a CG without a structured intervention, in the preparation of individuals with severe obesity who are candidates for BMS. Both models combine physical exercise and health education, focusing on improving functional capacity, exercise self-efficacy, quality of life, mental health, and sleep. The primary hypothesis is that the interventions will produce effects superior to those of the control and that the home-based model will exhibit greater adherence by eliminating logistical barriers, such as travel to the intervention site.

It is well established that prehabilitation has been established as a promising approach to optimize functional status and reduce perioperative risks [59,60]. In the context of obesity, studies have reported benefits including reduced BMI, improved physical fitness, enhanced respiratory muscle strength, and positive effects on metabolic parameters [61-65]. However, the literature is currently limited by high methodological heterogeneity regarding exercise type, duration, and intensity, which hinders standardization and limits comparability between studies [66,67].

Previous studies have demonstrated diversity in preoperative interventions for patients undergoing bariatric surgery, while also highlighting essential gaps in care. García-Delgado et al [15] tested respiratory training and measured outcomes related to preoperative weight, while the Bari-Active RCT [35] used a 6-week behavioral intervention with objective monitoring of PA, demonstrating benefits for quality of life. A recent review of home-based prehabilitation [68] indicated that home-based programs can reduce complications and improve functional performance, as well as symptoms of depression and anxiety. However, direct comparisons between home-based and in-person protocols, integrating objective measures of PA and mental health outcomes, are still scarce; this study addresses this gap by standardizing a multimodal intervention using FITT-VP principles, positioning it to resolve current inconsistencies in the evidence.

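### The significance threshold is misprinted as P<.0, and for HADS total the plan does not fix which contrast with control, at which visit, decides the primary hypothesis

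*Protocol article*

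**What the plan says.** All references are to the protocol article.

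- **Threshold.** Statistical Analysis states: "For all hypothesis tests, the α level for statistical significance will be set at" P"<.0, corresponding to a 95% confidence level". Sample Size Calculation uses another figure: "Considering an α level of .05 and power of .80".
- **Sized test.** The calculation concerns HADS total in three groups at three time points. An effect size f "of 0.25 (moderate) was assumed for the group × time interaction". The mixed model in Statistical Analysis contains that interaction, but the text does not call it the deciding test.
- **Hypothesis.** The Discussion states: "The primary hypothesis is that the interventions will produce effects superior to those of the control". It adds an expectation of better adherence in the home-based arm.
- **Multiplicity.** The only sentence on it says that secondary outcomes are exploratory and unadjusted. Nothing is said for the primary outcome, and no primary visit or pairwise contrast is named.
- **Home-based versus face-to-face.** Statistical Analysis and Intervention Program both treat this pair as a matter of estimation, read from effect estimates and confidence intervals.
- **Effect sizes.** Hedges g has this stated purpose: "To assess the magnitude of significant differences between the preintervention and postintervention moments and between groups".

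**The concern.** Three things in the text do not fit together.

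First, the sentence that governs every test carries a level that cannot be met and that differs from the level used to size the trial.

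Second, the test that was sized does not answer the question that was asked. A group × time interaction with three groups and three times can be significant because the two exercise arms differ from each other, because one arm worsens, or because a difference appears only at follow-up. A claim that the programmes beat control has to come from contrasts with control. The text does not say which contrasts, at which visit, or what counts as success when one is significant and another is not. The authors could then choose after seeing the data.

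Third, if g is given only for differences that reached significance, the published effects will be too large on average at this sample size, and later trials or meta-analyses that use them will inherit the error.

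**Working it through.** **Inputs.** From Sample Size Calculation: alpha .05, power .80, f = 0.25, k = 3 groups, m = 3 times, correlation ρ = 0.50, ε = 1.0, required N = 42 (14 per arm), 60 recruited (20 per arm). From Randomization and Blinding: 1:1:1. Assumed here: two-sided tests, contrasts taken as change from baseline, compound symmetry. The plan leaves the covariance structure to model fit.

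**1. The plan's own figure.** For the interaction, λ = f²·N·m/(1−ρ), df1 = (k−1)(m−1) = 2×2 = 4, df2 = (N−k)(m−1).
- N = 36: λ = 0.0625×36×3/0.5 = 13.5, df 4 and 66, power .823. This is the smallest equal-group N that reaches .80 (35 without equal groups).
- N = 42: λ = 15.75, df 4 and 78, power .887.

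The stated inputs therefore give 36, not 42; the same formula with two time points gives 42. The stated figure is conservative, and the present point does not depend on it. Dropout: 42/(1−0.30) = 60, as stated. The check confirms that the sized test is a single 4-df test.

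**2. How many contrasts could decide.** Three group pairs × two post-baseline visits = 6. Without home-based versus face-to-face: 2 × 2 = 4. At one visit: 2.

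**3. False-positive risk at .05.** Independent tests would give 1 − 0.95⁶ = 26.5%, 1 − 0.95⁴ = 18.5% and 1 − 0.95² = 9.75%. The contrasts are correlated because they share arms and the baseline. They were therefore simulated under the global null (100,000 trials per setting; 14 and 20 per arm; ρ 0.5 and 0.7; SE = √(4s²/n) with pooled within-person residual variance s²).

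| Rule for declaring success | Chance of at least one false positive |
|---|---|
| Interaction test alone | 5.0% |
| Six contrasts, only after a significant interaction | 4.7% |
| Two control contrasts, one visit | 8.9–9.2% |
| Three pairs, one visit | 11.9–12.2% |
| Two control contrasts, both visits | 15.8–16.1% |
| All six contrasts, ungated | 20.8–21.1% |

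**4. Would the interaction work as a gate?** The 4.7% holds only if neither programme has any effect. Suppose face-to-face works by 0.8 SD at both visits and home-based does nothing (assumed values). A gated analysis then declares a home-based versus control difference at one visit or the other in about 8% of trials (7.8% with 14 per arm, 8.5% with 20). If face-to-face works only post-intervention, at least one truly null contrast is declared in 13.2% or 15.0%.

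**5. The significance filter on g.** With SE = √(2/n) and cutoff c = t·SE, the mean g among significant results is about g + SE·φ(a)/(1−Φ(a)), where a = (c−g)/SE. For an assumed true g of 0.5:
- n = 14: SE = 0.378, c = 2.056×0.378 = 0.777, a = 0.733, mean = 0.5 + 0.378×1.316 = 1.00, or 2.0-fold.
- n = 20: SE = 0.316, c = 2.024×0.316 = 0.640, a = 0.443, mean = 0.5 + 0.316×1.100 = 0.85, or 1.7-fold.

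The factor depends on the true effect. By the same formula it is about 2.7 to 3.2 at g = 0.3 and about 1.2 to 1.4 at g = 0.8.

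**The case against.** The strongest reply has four parts.

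- **The threshold is recoverable.** The 95% confidence level and the .05 in the sample size section both identify it, and the nearby formula for g is also garbled, so a typesetting or text-reading loss is possible. This stands. A reader might infer that nothing could ever be declared significant and that the plan has no decision threshold; the document does not support that.
- **Six confirmatory tests are nowhere listed.** The one sized test has 5% error, the pair of exercise arms is set up for estimation, and the sentence on not adjusting concerns secondary outcomes. This also stands. A reader might infer a 21% error rate for the plan; that is the worst case of a range, not a rate the plan adopts.
- **Visit, contrast and multiplicity are often left to an analysis plan, and this is a condensed article.** True of the silence taken alone. It does not remove the mismatch within the article between an interaction test and a hypothesis of superiority over control, nor does the interaction used as a gate close it (step 4).
- **The text does not say that g is withheld for non-significant results.** It also defines bands for small and null effects, which a strict filter would leave nearly empty. This is fair, so the inflation follows from the wording as it stands and is not a declared intention. Home-based versus face-to-face is in any case to be read from estimates and intervals.

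**Conclusion.** The point holds in this form: a misprinted threshold that must be corrected, a primary hypothesis that the sized test cannot answer by itself, and effect sizes worded as following significance.

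The false-positive risk for the primary outcome lies between about 5% and 21%, according to a rule the document does not fix. For the contrasts the hypothesis names, it is about 9% at one visit and 16% over both. If both programmes must beat control at a single named visit, no inflation arises between those two contrasts. The hypothesis as worded does not settle whether both must succeed or either is enough.

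These figures assume two-sided .05, compound symmetry and change-from-baseline contrasts; they hardly move between ρ 0.5 and 0.7 or between 14 and 20 per arm. The 1.7- to 2-fold exaggeration rests on an assumed true g of 0.5 and on reading the wording as a strict filter.

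**What to change.** 1. Print the threshold as two-sided P<.05.
2. State before data are seen that home-based versus control and face-to-face versus control on HADS total, at one named visit (for example post-intervention), decide the primary outcome. Say whether either alone counts as success (then use Holm's procedure at familywise .05) or both must succeed (then no adjustment between them is needed).
3. Keep home-based versus face-to-face as an estimate with 95% CI, and make the other visit secondary.
4. Report model-based differences and g with 95% CI for every planned contrast, whatever its P value.

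The cost is wording only, but it should be settled well before the analysis planned for October to November 2026. There is a price in power. Under Holm the smaller P value is tested at .05/2 = .025. At an assumed g of 0.5, power for a single contrast falls from about 0.25 to 0.16 with 14 per arm, and from about 0.34 to 0.24 with 20 per arm. Requiring both contrasts avoids the split level, but the chance that both succeed cannot exceed the chance for either one.

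### Hedges g is tied to significant differences, so with 14 to 20 participants per arm the between-group values reported will overstate the true effect, and home-based versus face-to-face will probably get none

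*Protocol article*

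**What the plan says.** All of this is in the protocol article.

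- Statistical Analysis introduces Hedges g with the words "To assess the magnitude of significant differences between the preintervention and postintervention moments and between groups". No other sentence provides for g when a difference is not significant. The section then labels values below 0.2 as no effect, 0.2 to 0.4 as small, 0.5 to 0.7 as moderate and 0.8 or more as large.
- The same section sets the threshold: "the α level for statistical significance will be set at *P*<.0, corresponding to a 95% confidence level". Sample Size Calculation has "Considering an α level of .05 and power of .80".
- On the head-to-head contrast, Statistical Analysis says: "The home-based vs face-to-face comparison will be interpreted based on effect estimates and confidence intervals". Intervention Program gives the same aim: to estimate how far the two interventions differ, not to test equivalence.
- Sample Size Calculation requires 42 participants and recruits 60 to allow for 30% dropout. Randomization and Blinding allocates 1:1:1, which gives 14 or 20 per arm.

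**The concern.** An effect size shown only when its P value falls below a threshold is drawn from the upper tail of its sampling distribution. In small arms the significance boundary lies at a large standardized difference, so what passes is large whether or not the true effect is.

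Two things are at stake. First, a reader or meta-analyst who takes g from the report would get an exaggerated between-group value. The secondary outcomes are the most exposed, because there are many and they are analysed without multiplicity adjustment. Second, home-based versus face-to-face compares two programs with closely matched exercise prescriptions (Table 2). It is therefore the pair least likely to differ significantly, although magnitude is its stated purpose.

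**Working it through.** **Inputs.** Taken from the documents: α = .05, power .80, 3 groups, 3 time points, f = 0.25 for the interaction, ρ = 0.50, ε = 1.0, N = 42 required and 60 recruited, allocation 1:1:1. Assumed, because not stated: two-sided testing, equal SDs, and a two-sample t comparison standing in for the mixed-model contrast. At a correlation of 0.5, the SD of change is √(2(1 − 0.5)) = 1 raw SD, so the comparison of changes and the comparison of postintervention values have the same standard error.

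**Step 1: the plan's own sample size.** For the group × time interaction, λ = f²·N·m·ε/(1 − ρ), df1 = (k − 1)(m − 1)ε and df2 = (N − k)(m − 1)ε. With N = 36, λ = 0.0625 × 36 × 3/0.5 = 13.5, df = 4 and 66, and power is 0.823. With N = 33, power is 0.781. The stated inputs therefore need 35 participants, or 36 in equal groups, and the printed 42 is not reproduced (its power is 0.887). The dropout step is sound: 42/(1 − 0.30) = 60. The discrepancy is conservative and separate from this point. The planned 14 and 20 per arm are used below as they stand.

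**Step 2: smallest between-group g that can be significant.** g_min = J × t(.975, 2n − 2) × √(2/n), with J = 1 − 3/(4·df − 1).

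- n = 14, df 26: uncorrected minimum 0.777; J = 1 − 3/103 = 0.971; g_min = 0.75.
- n = 20, df 38: uncorrected minimum 0.640; J = 1 − 3/151 = 0.980; g_min = 0.63.

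No observed value in the protocol's small band (0.2 to 0.4) can pass at either size. The moderate band (0.5 to 0.7) cannot be reached at 14 per arm; at 20 per arm its upper part can.

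**Step 3: what is reported, given significance.** From 200,000 simulated two-arm comparisons per setting:

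| True effect | Significant, n = 14 / 20 | Mean absolute g if significant, n = 14 / 20 | Ratio to truth |
|---|---|---|---|
| 0.2 | 8% / 10% | 0.94 / 0.78 | 4.7 / 3.9 |
| 0.5 | 25% / 34% | 1.00 / 0.85 | 2.0 / 1.7 |
| 0.8 | 53% / 69% | 1.10 / 0.97 | 1.4 / 1.2 |

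With g reported every time, its mean for a true 0.5 is 0.50 at both sizes.

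**Step 4: within-group g (pre to post, correlation 0.5).** g_min = J × t(.975, n − 1)/√n.

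- n = 14: 0.577 × 0.941 = 0.54.
- n = 20: 0.468 × 0.960 = 0.45.

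**Step 5: sensitivity.** If the correlation were 0.7 (an assumption), the smallest significant between-group difference in raw SD units, using model degrees of freedom, is t × √(4(1 − 0.7)/n) = 0.58 at n = 14 and 0.49 at n = 20. The boundary falls but stays above the small band.

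**The case against.** The strongest reply is that g is a supplementary descriptor. The mixed model estimates within-group and between-group changes with no significance condition, and the head-to-head contrast is explicitly to be read from estimates and confidence intervals. The primary test and primary estimate are untouched. The text also states what g is for without saying that it is withheld otherwise. All of this stands and limits the point to g. The restriction to significant differences is an inference, though it is the plain reading, since no other use of g is given.

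Some stronger readings are tempting, and the documents do not support them:

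- A reader might infer that all reported effects will be inflated, or that the head-to-head contrast will have no effect estimate. The unfiltered model estimates rule out both. What that contrast would probably lack is a standardized g.
- A reader might infer that every published between-group g will be about 0.8 or larger. At 20 per arm, the planned randomized size, the floor is 0.63, and it is lower if the correlation is higher.
- A reader might infer that moderate effects can hardly ever be reported. A true between-group 0.5 passes in 25% to 34% of trials, although overstated when it does, and moderate pre-to-post values can be reported.
- A reader might take P<.0 literally, as a threshold that nothing can meet. The same sentence gives a 95% confidence level and the sample size section uses .05, so it is a misprint. It plays no part in the inflation.

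The gaps between the bands close if g is rounded to one decimal. The small-sample factor missing from the condensed formula is worth only 2% to 3%. Neither adds weight.

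**Conclusion.** The point holds for Hedges g and no further. As worded, the plan selects g by significance. For true between-group effects of 0.5 to 0.8, the mean reported value would be about 1.2 to 2 times the truth at 14 to 20 per arm, and the overstatement is larger for smaller true effects. The size rests on two-sided .05, equal SDs and a two-sample approximation at correlation 0.5. A higher correlation lowers the boundary, but the bias remains for as long as the selection does. That home-based versus face-to-face would go without g is probable rather than certain; it rests on the similarity of the two programs. This is a reporting rule worth changing before analysis. It is not a flaw in the primary analysis.

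**What to change.** In Statistical Analysis, replace the reference to significant differences with a statement that Hedges g and its 95% confidence interval will be calculated and reported for all planned pairwise contrasts (home-based vs control, face-to-face vs control, home-based vs face-to-face) at postintervention and at follow-up, regardless of the P value. Correct the threshold from P<.0 to P<.05 so that it agrees with Sample Size Calculation. The cost is a change of wording and a few more reported numbers. It needs no additional participants, data or tests.
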